The objective of this randomized, double-blind, placebo-controlled, parallel-group clinical trial is to evaluate the efficacy and safety of HSF extract on sleep improvement in adults with sleep discomfort and to compare them with that of placebo. Eighty participants will be randomly allocated to the HSF extract or placebo groups in a 1:1 ratio. The superiority of the HSF extract over placebo will be tested.

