### 2.4. Outcomes

#### 2.4.1. Primary outcome

The primary outcome of this study is the change from the baseline of the PSQI (29, 30) global score after 4 weeks of administration. The PSQI is a representative self-rated questionnaire that assesses sleep quality and disturbances for over a month. A higher PSQI global score indicates poor sleep quality.

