### 2.5. Sample size

The primary objective of this clinical trial is to evaluate the superiority of the PSQI global score improvement in the HSF extract group compared to that in the placebo group. To estimate the mean difference of the PSQI global score between both groups and the pooled standard deviation, the results of a previous randomized trial (35) will be used to assess the PSQI global score. In the earlier trial, the mean difference of change from baseline between the two groups was −3.95 (−3.96 in the treatment group and − 0.01 in the placebo group). The standard deviation of the change from baseline was not presented, and the largest value of the standard deviation of the PSQI global score was 3.4. To calculate the sample size for this study, the mean difference and pooled standard deviation were estimated as −2.50 and 3.4, respectively. With a 5% level of significance, 80% power of the test, and 25% dropout rate, the required sample size for each group was calculated as 40.

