#### 2.11.2. Statistical method for analyzing primary and secondary outcomes

The change from the baseline PSQI global score at 4 weeks between the two groups will be compared using a two-sample *t*-test or Wilcoxon rank sum test, according to the normality of data. Additionally, changes in the PSQI global score over time in each group will be compared using a paired *t*-test. A generalized linear model (GLM) with covariates of caffeine consumption, age, body mass index, smartphone usage time, and drinking habits can also be conducted. In case of significant differences in baseline characteristics between the two groups, these baseline characteristics can be considered as covariates in conducting the GLM.

The statistical method used for analyzing secondary outcomes is identical to that used to analyze the primary outcome.

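### A normality check chooses between a mean and a rank comparison for the primary outcome, and baseline PSQI is adjusted for only if it happens to differ significantly

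*Protocol article*

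**What the plan says.** Section 2.4.1 of the protocol article defines the endpoint: "The primary outcome of this study is the change from the baseline of the PSQI" global score, at 4 weeks. The Introduction sets the hypothesis: "The superiority of the HSF extract over placebo will be tested".

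Section 2.11.2 then makes three statements of different standing.

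- The between-group comparison will use a two-sample t-test or a "Wilcoxon rank sum test, according to the normality of data". The article does not name the normality test, its threshold or the variable examined.
- A GLM "with covariates of caffeine consumption, age, body mass index, smartphone usage time, and drinking habits can also be conducted". This is worded as optional. Baseline PSQI is not on the list.
- More covariates may enter that GLM: "In case of significant differences in baseline characteristics between the two groups, these baseline characteristics can be considered as covariates in conducting the GLM". This too is optional.

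For the other endpoints: "The statistical method used for analyzing secondary outcomes is identical to that used to analyze the primary outcome".

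The sample size in section 2.5 rests on means: "the mean difference and pooled standard deviation were estimated as −2.50 and 3.4, respectively".

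**The concern.** There are two separate problems.

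First, a t-test and a Wilcoxon test do not address the same quantity. One compares mean change; the other compares ranks. Section 2.5 plans for a mean difference of 2.5 points, so in one branch the trial would test something other than the quantity it was designed around, and the observed data would decide which.

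Second, in a properly randomised trial a significant baseline difference is a chance event and says nothing about whether the variable predicts PSQI change. A rule built on it adjusts for irrelevant variables that happen to differ and leaves out prognostic ones that happen not to. The variable most likely to matter for a change score is its own baseline value, and here it can enter only through this rule.

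The article also does not say how the optional GLM ranks against the unadjusted test if the two disagree. The results are meant to support a health claim to the regulator (section 4.4), and the secondary outcomes inherit the same scheme.

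**Working it through.** **1. The plan's own figure.** Inputs from section 2.5: difference 2.5, SD 3.4, 5% level (taken as two-sided), 80% power, 25% dropout.

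n = 2 × (1.960 + 0.842)² × 3.4² / 2.5² = 29.03, so 30 per arm; 30 / 0.75 = 40. The stated 40 reproduces, and it is a calculation for a difference in means.

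**2. Type I error.** Simulated with 30 evaluable per arm, SD 3.4, scores rounded to whole points and five independent covariates. The outcome-covariate correlation was 0.3 or 0.5; errors were normal, skewed or heavy-tailed; there were 5,000 null trials per setting (Monte Carlo SE about 0.3 percentage points). The normality check was Shapiro-Wilk at 5% in each arm. All these settings except the SD and the 30 per arm are assumptions.

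| Practice | Type I error |
|---|---|
| One fixed analysis (t, Wilcoxon or five-covariate GLM) | 4.2% to 5.1% |
| Normality switch, followed strictly | 4.5% to 5.4% |
| More favourable of t and Wilcoxon | 5.2% to 6.2% |
| Switch result or five-covariate GLM, whichever is significant | 6.3% to 8.0% |
| Any of t, Wilcoxon, fixed GLM, GLM with significant covariates | 6.9% to 9.1% |

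In a second set of null runs, which modelled baseline and follow-up PSQI explicitly (SD 3.4 each, correlation 0.3, 0.5 or 0.7), the strict switch rejected in 4.9% to 5.2%. Taking the best of the open analyses, with baseline PSQI entering only when significantly different, gave 6.8% to 7.3%.

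**3. How often the switch changes the quantity tested.** With normal errors, the Shapiro-Wilk check still sent 17% to 18% of trials to the Wilcoxon test. With skewed or heavy-tailed errors it sent 56% to 86%.

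**4. The baseline-significance rule.** With k independent characteristics each tested at 5%, the chance of at least one significant difference under correct randomisation is 1 − 0.95^k. This is 23% for k = 5, 40% for k = 10 and 54% for k = 15. The article does not give k, so these values are assumed.

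The largest non-significant baseline PSQI gap, with 40 per arm and an assumed baseline SD of 3.4, is 1.991 × 3.4 × √(2/40) = 1.51 points. It scales with the SD: at an assumed SD of 2.5 it is 1.991 × 2.5 × √(2/40) = 1.11.

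The endpoint already subtracts baseline, so only regression to the mean is left. With equal SDs and correlation ρ, a gap g shifts the change-score difference by (1 − ρ) × g. For g = 1.51 this is 1.06, 0.75 or 0.45 points at ρ = 0.3, 0.5 or 0.7. The middle value is 0.75 / 2.5 = 30% of the planned effect.

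**5. What adjustment would gain.** With SD 3.4 at each time and 30 per arm, the SD of change is 3.4 × √(2(1 − ρ)) and the ANCOVA residual SD is 3.4 × √(1 − ρ²). Power follows from a noncentral t with noncentrality 2.5 / (SD × √(2/30)).

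| ρ (assumed) | SD of change | Residual SD | Power, t-test: formula (simulated) | Power, ANCOVA: formula (simulated) |
|---|---|---|---|---|
| 0.3 | 4.02 | 3.24 | 66% (66%) | 84% (83%) |
| 0.5 | 3.40 | 2.94 | 80% (79%) | 90% (88%) |
| 0.7 | 2.63 | 2.43 | 95% (95%) | 97% (97%) |

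The simulated figures run slightly lower in places because the formula ignores chance baseline imbalance and rounding. Simulated ANCOVA type I error was 5.0% to 5.3%.

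**The case against.** The best defence is that the plan does have a rule. Normality selects one of two tests, that test gives one primary p-value, and the GLM is plainly an addition. Which normality test is used, and at what threshold, is detail that a SAP may hold.

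Much of this stands. A reader might infer that the baseline tests select the confirmatory analysis. They do not: that rule governs only the optional GLM. A reader might also infer that the 5% level fails under the plan as written. It does not, because the switch followed strictly stays near 5%. The 7% figure needs an analyst who claims the best of several results, and nothing in the article describes that practice. A figure of about 9.5% can be produced by putting baseline PSQI into the GLM in every trial and then choosing the best result, but the article allows it in only when it differs significantly.

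It is also true that the switch costs no power in the settings tried. At a 2.5-point difference it rejected in 80% of trials with normal errors, as the t-test did, and in 87% with skewed errors, against 80% for the t-test.

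The appeal to an unseen SAP does not dispose of the point. The article does not leave the choice open; it states a data-dependent rule and a significance-based covariate rule, and a SAP that follows it would carry both over.

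**Conclusion.** The point holds as a fault in how the analysis is fixed, not as a failure of error control. The primary test can move from a mean difference to a rank comparison on the strength of the trial data, while the sample size is for a mean difference. Baseline PSQI is left out unless chance makes it differ significantly. At an assumed SD of 3.4 and correlation of 0.5, that could leave up to about 0.75 points of a 2.5-point planned effect unadjusted without triggering the rule. Type I error is near 5% if the rule is followed, and about 7% (6% to 9% over the assumed settings) only if the most favourable open analysis is claimed.

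The size depends on assumptions outside the article: the correlation, the baseline SD, the number of characteristics tested and the normality test used. The 3.4 is the largest PSQI SD from another trial; the entry limits on PSQI and ISI here may narrow the spread at baseline. The sample size is not in question.

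**What to change.** - Name one primary analysis regardless of normality: the mean difference between groups in 4-week PSQI change, adjusted for baseline PSQI (ANCOVA), with a 95% CI. State that this result decides superiority.
- Make the Wilcoxon test and the five-covariate GLM sensitivity analyses that are always run and always reported.
- Delete the rule that adds covariates on baseline significance.
- Carry the same structure to the secondary outcomes, each adjusted for its own baseline value.

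Adjusting for site and adding a permutation test are reasonable but optional.

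The cost is wording, in the SAP or an amendment before unblinding. Baseline PSQI is already collected, the 40 per group need not change, and power at the planned effect rises.

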### 2.12. Data monitoring and auditing

The estimated risk of the trial is low because the investigational product of this trial is a food. A data monitoring committee is not required and an interim analysis is not planned.

A contract research organization hired by sponsors will monitor the clinical trial to verify the process of informed consent acquisition, conduct the trial in compliance with the approved protocol, and obtain accurate and complete trial data. The initial monitoring visits for each site are scheduled within 7 days of the enrollment of the first participant. Routine monitoring will also be conducted 10–11 times at each site.

### 2.13. Harms

Adverse events will be carefully assessed through non-directive questioning during the trial period. The symptoms and signs of adverse events in participants will be collected at every visit, and their severity and causality will be assessed. Blood and urine tests will be conducted before and after the intervention, and clinically significant abnormal results will be assessed. Owing to the characteristics of the investigational product as a health functional food, product-related severe adverse events are not expected, and mild dyspepsia may occur.

## 3. Discussion

This clinical trial aims to test the potential of HSF extract as functional food for sleep improvement in humans. Approximately one-third of the general population has low-quality sleep, whereas approximately 6–15% of the population is diagnosed with insomnia disorders (5). Some people who complain of insomnia may not require sleep medicine if their symptoms are not severe enough, and may instead benefit from functional food that can help improve their sleep quality. This protocol was developed to evaluate the functionality of HSF extract in improving sleep quality in that population. Patients with severe insomnia, depressive or anxiety disorders, and other sleep disorders are set to be excluded from this trial. Furthermore, a large effect size of health functional foods may not be obtained, and we have tried to exclude confounding factors as much as possible. Strict exclusion criteria will be applied, and participants with irregular sleep patterns due to night shifts, smoking, heavy caffeine or excessive alcohol consumption are set to be excluded. In addition, the eligibility criteria and outcomes in this trial have been planned according to the Korean MFDS functionality test guideline for health functional food that “may help to improve sleep quality” (39).

Regulations governing functional foods differ between countries. In the United States, there are three categories of health-related claims: nutrient content claims, structure/function claims, and health claims (40). However, sleep-related statements are not included in the health claims category. For instance, while valerian-containing products are promoted as sleep aids (12), they fall under the structure/function claims category and must carry a label indicating that they are not intended to diagnose, treat, cure, or prevent any disease (40, 41). In Japan, there are three types of functional foods: those with nutrient function claims, those with specified health uses, and those for special dietary uses. Since 2015, sleep-related health claims have been added to new functional products, making them one of the major health claims (42).

In Korea, functional ingredients are divided into two categories: those that have been notified by the Ministry of Food and Drug Safety (MFDS) and those that undergo individually recognized by the MFDS (43). The former includes 95 types of functional ingredients, such as vitamins, minerals, essential fatty acids, protein, dietary fiber, ginseng, and green tea extract (44). For an ingredient to obtain individual recognition as a functional ingredient, the applicant should submit data on the ingredient’s safety and functionality. The MFDS then reviews the data consults with the Health Functional Food Deliberation Committee before making a decision on recognition (45). “May help to improve sleep quality” is one of the health claims included in the individual recognition as a functional ingredient category. This trial aims to test the potential of HSF extract to obtain individual recognition for improving sleep quality.

This study protocol has some limitations. First, this is the first human study on the effect of HSF extract on sleep improvement, and no previous study has calculated the effect size of HSF extracts. Therefore, we estimated the effect size of HSF extract on sleep improvement based on the results of a previous randomized trial with a similar design. Second, there are some limitations to measuring sleep using PSG in the hospital for a single night (46, 47). Although an actigraphy device would be a good option for monitoring sleep patterns in a home environment, we could not select it due to budget constraints. To complement this, a sleep diary will be maintained and various sleep characteristics extracted from both PSG and the sleep diary will be considered. We will collect a wide range of data regarding sleep using questionnaires, PSG, and blood biomarkers; this is one of the strengths of this trial. Third, due to a delay in administrative procedures, this protocol was registered on the international clinical trials registry platform after the first participant enrolled. Nevertheless, the protocol was registered at the early stage of the trial, and the registered protocol version is the same as the version at the time of enrollment of the first participant.

## 4. Ethics and dissemination

### 4.1. Research ethics approval

This protocol was approved by the Institutional Review Boards (IRB) of Kyunghee University Hospital at Gangdong (IRB No. KHNMC 2021–11-024) and Keimyung University Dongsan Hospital (IRB No. DSMC 2021-11-07). In case protocol amendments are required, before applying the changes, approval from both the IRBs will be obtained for the revised version of the protocol. The current version of the protocol is 1.2 (date: 2022-01-10).

### 4.2. Consent or assent

Prior to the screening process, investigators delegated by the principal investigators will provide sufficient information on this clinical trial, and participants will have adequate time to decide whether or not to participate in this clinical trial. If a person decides to participate voluntarily, written informed consent will be obtained from them.

### 4.3. Confidentiality

To protect the confidentiality of participants, the initial and not the name of each participant will be entered into the eCRF, and each participant will be identified by the screening number of this trial. The two sponsoring institutes (Korea Institute of Oriental Medicine and Dongkook Pharmaceutical) will have access to the final trial dataset, and a blind review will be conducted to confirm the analysis set before the data is locked.

### 4.4. Dissemination policy

The research findings will be submitted to and published in peer-reviewed journals. In addition, the efficacy and safety results of this trial will be submitted to the Korean MFDS for individual recognition of the new functional ingredient as one that “may help to improve sleep quality.”

## Ethics statement

The studies involving human participants were reviewed and approved by the Institutional Review Board of Kyunghee University Hospital at Gangdong and the Institutional Review Board of Keimyung University Dongsan Hospital. The patients/participants provided their written informed consent to participate in this study.

